### Dietary counselling

All participants will undergo face-to-face dietary education and counseling with a qualified dietitian in line with evidence-based guidelines [21], incorporating standard pre-dialysis education during the first week of run-in (Figure 1). Specifically, the goal of the intervention provided will be to target intake in line with current recommendations [22], including protein intake at 0.8 g/kg/day and to establish baseline dietary fibre intakes. In the week following, and throughout the intervention, patients will be encouraged to maintain stable protein and fibre intakes, with specific attention to maintaining the same sources of these nutrients (ie. animal vs. plant protein and soluble vs. insoluble fibre). Participants’ dietary intakes and adherence to a stable diet during the study will be assessed using a multi-method approach to optimize accuracy of dietary intake estimates while minimizing patient burden. An open-ended, structured diet history method will be used to establish usual intake at baseline and the end of each intervention period. This method is considered ideal for capturing usual intake over a predefined period of time. In order to limit recall bias, a self-administered diet history will be used based on a template completed prior to the interview [23], and verified by the same dietitian in a face-to-face interview. A 24 hr recall, according to the US Department of Agriculture multiple pass method [24], will be employed to assess the stability of dietary intake throughout the study. This less time-intensive dietary assessment method was chosen to limit participant burden. Both diet assessment methods will utilize food models to increase the accuracy of estimated portions, particularly protein and fibre sources. Dietary data will be entered into Food Works 7 (Xyris Software, version 7.0.2915) using the Australian Food, Supplement and Nutrient database (AUSNUT) 2007 (for key macro- and micronutrients) and NZ Foodfiles 2010 (to quantify soluble fibre and amino acids, not available in AUSNUT). In addition, dietary protein intakes will be verified according to the formula by Maroni et al. [25] using 24 hr urinary urea nitrogen and body weight [26].

### Randomisation

Computer-generated randomisation of participants to treatment order will be undertaken by an external statistical consultant. This process of allocation will conceal the randomisation order to researchers and participants. In addition, the supplements will be packed off-site with a generic label, supplement A or B, for the first and second intervention, respectively.

### Pre- and probiotic intervention

The underlying rationale for selecting the bacterial strains in the synbiotic formulation is the mechanistic inhibition of bacterial production of IS and PCS (detailed in Table 1) [27]. Importantly, the bacterial strains selected should have limited, if at all, enzymatic capacity to produce IS and/or PCS and ideally displace bacteria that do. On the basis of these criteria, strains from the Lactobacillus and Bifidobacteria genera present themselves as suitable candidates for the purpose of this trial [28-30].

A strain from the *Streptococcus thermophilus* species is also considered an important component in the synbiotic formulation due to its high urease capacity. In fact, a previous study in the CKD population reported a significant decrease in blood urea nitrogen (BUN) with the inclusion of this species in the probiotic formula [31]. Hence, the probiotics in this study will contain strains from the Lactobacillus, Bifidobacteria and Streptococcus genera.

The prebiotic component will include high molecular weight inulin (inulin HP), fructo-oligosaccarides (FOS) and galacto-oligosaccarides (GOS), based on a number of mechanistic benefits described in Table 1[32,33]. In addition, the literature suggests the production of IS and PCS occurs in both the proximal and distal sections of the colon. Therefore, in order to target and diminish the colonic production of these toxins, a prebiotic product that facilitates fermentation throughout the entire colon is ideal. FOS and GOS both have small degrees of polymerisation (DP) (DP < 10) and therefore are completely fermented in the proximal part of the colon. The addition of inulin HP with a DP ranging from 10–60 may assist the extension of the fermentation to the distal part of the colon [34].

In order to ensure the validity of the formulation, only fibre varieties that have gone through the rigorous process of attaining prebiotic status, as defined by Gibson et al. will be included [35].

### Supplement dosing and duration

The synbiotic intervention will be a daily dose of 15 grams of prebiotics, including a combination of 3 different types of fibres, and the probiotic component will include 90 billion colony-forming units (CFU) from 9 different strains across the Lactobacillus, Bifidobacteria and Streptococcus genus. There is no consensus as yet on adequate dosing or duration of synbiotics due to the diversity of GI survival rates of probiotic strains and the different characteristics of prebiotic varieties, such as their bifidogenic capacities [33]. Nevertheless, the available evidence suggests that there maybe be a threshold dose and duration required to see a benefit for lowering IS and PCS production [19]. The dosing of pre- and probiotics used in SYNERGY is based on previous successful trials [30,36,37]. However, in order to minimise the side effects reported in previous studies, such as flatulence and bloating [38], the synbiotics will commence at half dose for the first 3 weeks.

The durations of most intervention studies in this area have been ≤4 weeks, with one study demonstrating no benefit comparing 4, 8 and 12 week intervention periods [37]. The intervention period for SYNERGY is a 6 week duration to allow time for dose escalation, minimise symptom burden and establish whether there is a dose-dependent and sustained benefit of the therapy.

### Primary outcome

#### Serum indoxyl sulphate

Venous blood will be collected following an overnight fast at 7 time points throughout the study, see Table 2. Samples will be centrifuged at 3000 rpm for 10 mins before being stored at −80°C. Samples will be batched and sent for analysis of serum concentration of IS, total and free, using an ultra-performance liquid chromatography (UPLC) and fluorescence detection method. This recently validated method will allow for low limits of detection down to 0.1 μmol/L and has been described in detail by Pretorius et al. [39]. This method will also be followed for PCS.

**Table 2 T2:** SYNERGY data collection schedule

		**Run-in Week −2**	**Intervention A & B**		
			**Baseline**	**Mid point**	**End point**
			**Week 0 & 11**	**Week 3 & 14**	**Week 6 & 17**
**Serum uremic toxins**	Indoxyl sulphate (free and total)	X	X	X	X
	P-cresyl sulphate (free and total)	X	X	X	X
**Cardiovascular risk**	Oxidative stress		X		X
	Inflammation		X		X
	Endotoxemia (lipopolysaccharide)		X		X
**Kidney damage**	24 hr albuminuria and protienuria		X		X
	Kidney injury molecule-1		X		X
	Estimated glomerular filtration rate	X	X		X
**Dietary**	Diet history interview	X			X
	24 hr recall		X	X	
	24 hr urinary urea nitrogen		X		X
**Quality of life**	Short Form-36				X
**Gastrointestinal symptoms**	Gastrointestinal symptom rating scale	X		X	X
**Gut microbiota**	Fecal sample (optional)		X		X
**Compliance**	Pill count			X	X
**Dose escalation**				X	

Participants will be provided with a standard evening meal preceding their overnight fast before each blood collection. This is a precautionary measure to minimise any potential residual influences of the macronutrient distribution of proximal meals on participants’ serum IS and PCS levels.

### Secondary outcomes

#### Endotoxemia

Plasma samples will be collected in endotoxin-free vials following each intervention and stored at −80°C. Quantification of lipopolysaccharides will be undertaken using a Limulus Amebocyte assay (Cambrex, Verviers, Belgium), as described previously [40].

#### Trimethylamine-N-oxide

TMAO and its precursor, trimethylamine (TMA), will be extracted from plasma with Acetonitrile-containing labelled internal standards. The supernatant will then be injected into a Waters UPLC system and separated under reverse phase conditions. The column eluent will be introduced into a Waters TQD Tandem Mass Spectrometer and specific Multiple Reaction Monitoring (MRM) will be carried out for each of the analytes.

#### Inflammation and oxidative stress

A panel of inflammatory markers, including interleukin-6 (IL-6) and tumor necrosis factor-α (TNFα), will be measured in serum samples before and after each intervention using electrochemiluminescence immunoassay techniques. Selection of these markers was based on their regulatory association with Nuclear Factor-kappaB (NF-kB) [41] and their association with IS and PCS in the CKD population [42].

In addition, markers of lipid oxidation (total F_2_ isoprostanes) and endogenous antioxidant activity (glutathione peroxidase (GPx)) will be measured to provide a comprehensive assessment of potential pathways involved in the toxicity of IS and PCS . These biomarkers will be measured in plasma samples using validated methods [43,44].

#### Kidney damage

SYNERGY will include kidney damage as a secondary outcome using 24 hr urine samples (gold standard) for measuring proteinuria and albuminuria [45]. Participants will be provided with bottles for collection and educated on correct collection procedures in accordance with standard protocol. Urinary total protein (pyrogallol red) and urinary albumin (turbidimetric method based on antibody-antigen complexes) will be measured in timed-samples (mg/24 hrs) and cross-checked against creatinine ratios (protein and albumin, respectively) on Beckman DxC800 general chemistry analyser (Beckman Coulter, Brea, CA, USA) [46].

Kidney function using the Chronic Kidney Disease Epidemiology Collaboration (CKD-EPI) formula will also be measured [22].

In addition, urinary Kim-1, a marker of kidney tubule damage, will be measured from midstream urine collections before and after each intervention [47]. Samples will be stored at −80°C, followed by analysis using a commercially available sandwich ELISA according to the manufacturer’s instructions (USCN Life Sciences, Wuhan, PRC). Significant changes in Kim-1 have been achieved in a 6 week dietary intervention study indicating the feasibility of Kim-1 as a sensitive marker in SYNERGY [48].

#### Quality of life

QOL will be assessed in SYNERGY by the validated Short Form-36 (SF-36), which has been used widely in renal populations [49,50].

#### Gastrointestinal symptoms

Monitoring GI symptoms in SYNERGY has two purposes, safety monitoring and hypothesis generation. The validated Gastrointestinal Symptom Rating Scale (GSRS) will be administered at baseline, mid-point (prior to dose escalation), and the end of each intervention [51]. The GSRS data will be presented as a total score and as dimension scores (reflux, pain, indigestion, constipation and diarrhoea) [52].

#### Safety and adherence

All serious adverse events will be reported to the ethics committee, whether deemed to be supplement related or not. In addition, medical officers will cross-check all blood and urine results during the study. Adherence to supplements will be measured by pill count and powder weight at both the mid point and end of each intervention.

### Exploratory outcome

#### Gut microbiota

A microbial analysis will be an opt-in component to SYNERGY. Fecal samples will be collected according to standard procedures and stored at −80°C prior to batch analysis pre and post each intervention. Microbial DNA extraction will be performed using published methods [53] and the abundance of key probiotic bacteria measured by species-specific qPCR methodologies. These specific bacteria as well as alpha- and beta-diversity measures will be derived from barcoded amplicon libraries of the V4 hypervariable region (517 F-803R) of the prokaryote *rrs* genes present in each sample, using protocols similar to those described by Caporaso et al. [54]. The libraries will be sequenced using the Illumina MiSeq platforms, and following demultiplexing and initial sequence quality control assessments, analyzed using the Quantitative Insights Into Microbial Ecology (QIIME) pipeline (qiime.sourceforge.net) as described by Caporaso et al. [55]. Enzymes relevant to the primary outcome of the study (namely tryptophanase and 4-hydroxyphenylacetate decarboxylase, which catalyze the production of IS and PCS, respectively) will also be measured. This is vital for proof of concept exploration and to provide insight for refinement of the synbiotic formulation.

### Statistical analysis

Preliminary data from a cohort of CKD Stage IV-V (pre-dialysis) patients recruited from the same Nephrology department were used for power calculations. The mean serum concentration of IS in this population was 14 μmol/L with a mean intra individual standard deviation of 4 μmol/L between 3 measurements over a 6 week period (unpublished data from [name] and [name]). With 1:1 randomisation, SYNERGY will require 24 participants to complete the study. This sample size is based on a 30% reduction in IS levels; alpha of 5% and power of 90%. Allowing for a 20% drop out and using the adjustment factor 1/1(1-υ)^2^, a total of 37 participants will be recruited. This magnitude of change is related to a significant improvement in kidney function [56]. Furthermore, a reduction in IS concentration of this size has been achieved in previous probiotic intervention studies and is therefore considered a realistic target [57].

The primary analysis of IS concentrations will be undertaken using an independent t-test with treatment sequence allocation as the independent variable and the difference between serum concentrations measured after the first and second treatment as the dependent variable [58]. Secondary analysis of the primary outcome will include mixed modelling to account for missing data and to determine whether there is a dose dependent effect of the synbiotics.

In addition to the widely used diversity metrics and analysis tools available via QIIME, permutational multivariate analysis of variance (PERMANOVA) will be conducted on the genus level operational taxonomic units (OUT) tables to test the relationships between the stool microbiome and the primary and secondary outcomes of the study. Constrained ordination methods, such as analysis with respect to instrumental variables, will also be carried out [59].

Previous studies in pre-dialysis populations suggest a high incidence of antibiotic prescription secondary to high comorbidity burden, susceptibility to urinary tract infections, and prophylactic use for surgical procedures. Because this is a proof-of-concept study and the use of antibiotics may confound the mechanisms underpinning the synbiotic therapy, sensitivity analyses will be undertaken including and excluding patients prescribed antibiotics during either intervention arm. In addition, further analysis will be undertaken to assess whether there is a treatment order effect. The null hypothesis will be rejected at the 0.05 level. The statistical analyses will be performed using Stata (version 12, 2012, Statacorp, College Station, TX).

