**Methods/design:**

Thirty-seven patients with moderate to severe CKD (Stage IV and V, pre-dialysis) will be recruited to a double-blind, placebo-controlled, randomised cross-over trial. Patients will be provided with synbiotic therapy or placebo for 6 weeks, with a 4 week washout before cross-over. The primary outcome is serum IS, total and free (unbound) concentrations, measured using ultra-performance liquid chromatography. Secondary outcomes include serum PCS, total and free (unbound) concentrations; cardiovascular risk, measured by serum lipopolysaccharides, serum trimethylamine-N-oxide (TMAO) and inflammation and oxidative stress markers; kidney damage, measured by 24 hour proteinuria and albuminuria, estimated glomerular filtration rate and renal tubule damage (urinary kidney injury molecule-1); patients’ self assessed quality of life; and gastrointestinal symptoms. In addition, the effects on the community structure of the stool microbiota will be explored in a subset of patients to validate the mechanistic rationale underpinning the synbiotic therapy.

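### The recruitment target of 37 applies a squared dilution factor to plain drop-out; the stated 24 completers and 20% drop-out give 30

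*Protocol article*

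**What the plan says.** The Statistical analysis section of the protocol article sets the requirement in terms of finishers: "SYNERGY will require 24 participants to complete the study". The inputs are given in the same paragraph. On the outcome level it says: "The mean serum concentration of IS in this population was 14 μmol/L". For variability it gives a within-person SD of 4 μmol/L, from three measurements spread over six weeks. The target effect is a 30% reduction, with alpha 5% and power 90%; allocation is 1:1 to treatment order.

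The step from finishers to recruits reads "Allowing for a 20% drop out and using the adjustment factor" followed by the expression 1/1(1-υ)^2, and ends with "a total of 37 participants will be recruited". The abstract repeats the number: "Thirty-seven patients with moderate to severe CKD".

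The next paragraph of that section defines the primary analysis. It is an independent t-test between the two treatment sequences, and the dependent variable is each participant's difference between the serum concentrations after the first and after the second treatment. Mixed modelling to deal with missing data is listed as a secondary analysis of the primary outcome.

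**The concern.** Two different problems call for two different inflation factors. If a fraction υ of participants disappears from the analysis, the number recruited is the number needed divided by (1-υ). If that fraction stays in the analysis but shows no treatment effect, the mean effect shrinks by (1-υ). Because sample size varies with the inverse square of the effect, the divisor is then (1-υ)^2.

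The plan describes the first problem and uses the factor for the second. Its primary test settles which applies: a participant lacking either end-of-treatment value has no difference to enter, so drop-out reduces the number analysed and does not dilute the effect. Nothing in the article says that drop-outs are retained or imputed in the primary test.

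At stake is whether the headline recruitment figure follows from its stated inputs. If it does not, a reader cannot tell what the extra patients are for, and a single-centre trial asks more patients than it has justified to follow a schedule that runs to week 17 after a run-in.

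**Working it through.** **Inputs (all from the Statistical analysis section).** Completers 24; drop-out υ = 0.20; mean IS 14 μmol/L; within-person SD 4 μmol/L; reduction 30%; alpha 5%; power 90%. The article does not say whether alpha is one- or two-sided; two-sided is assumed.

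**Step 1: reproduce the 24.**
- Effect: 0.30 × 14 = 4.2 μmol/L.
- SD of a within-person difference: 4 × √2 = 5.66 μmol/L.
- Normal approximation for the total N of a two-period cross-over: N = 2 × 4² × (1.960 + 1.282)² / 4.2² = 19.06, so 20.
- Exact power of the two-sequence t-test (noncentral t, N − 2 degrees of freedom, noncentrality 4.2 / (5.66/√N)): N = 20 gives 88.1%, N = 22 gives 91.2%, N = 24 gives 93.5%.

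The exact requirement is 22. The stated 24 is within two patients of it and is not in dispute.

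**Step 2: reproduce the 37.**
- Squared factor: 24 / (1 − 0.20)² = 24 / 0.64 = 37.5.

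The stated 37 is this value rounded down, so the squared factor was in fact used and the printed 1/1(1-υ)^2 is a misprint of it.

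**Step 3: the factor that matches drop-out.**
- 24 / (1 − 0.20) = 24 / 0.80 = 30.
- Check: 30 × 0.80 = 24 completers, as required.
- Excess: 37 − 30 = 7 patients, and 7/30 = 23%.

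**Step 4: what 37 delivers.**
- Completers at 20% loss: 37 × 0.80 = 29.6, so about 29.
- Loss that would leave exactly 24: 1 − 24/37 = 35.1%.

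| Completers | Power (fall 4.2, within-person SD 4, two-sided 5%) |
|---|---|
| 22 | 91.2% |
| 24 | 93.5% |
| 29 | 97.1% |
| 30 | 97.5% |

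**Step 5: what the extra patients could buy (assumed scenarios, not in the article).**
- Within-person SD 4.5 instead of 4: 24 completers give 87.1%, 29 give 92.9%.
- A true 20% dilution, with the effect falling to 0.8 × 4.2 = 3.36: 30 analysed give 88.1%, 37 analysed give 94.0%.

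**The case against.** The strongest reply is that the error does no statistical harm. The 24 is a minimum; 37 recruits with 20% loss exceed it, and power is above the required 90%. Type I error, the analysis and its interpretation are unaffected. All of that stands, and it is why the point ranks as a correction and no more.

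A second reply is that the margin may be deliberate. The Background notes that poor compliance may have contributed to a negative trial of an oral adsorbent. The Safety and adherence section measures adherence. The end of the Statistical analysis section expects frequent antibiotic prescription and plans sensitivity analyses that leave those patients out. Each would be a fair reason to recruit beyond 30, and the scenarios with a larger SD or a diluted effect show that the margin would be useful. But the article links none of them to the 37. It labels the allowance as drop-out.

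Two stronger readings are tempting and should be set aside:

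- A reader might infer that 37 follows from no formula at all, because 37.5 would normally be rounded up to 38. That is not supported. The figure plainly comes from the squared factor, and the gap is half a patient. The article does not print the calculation behind 24, and an unrounded requirement of, say, 23.5 would round up to 24 completers and, divided by 0.64, give 36.7, so 37.
- A reader might infer that the stated size, drop-out and power are mutually impossible. They are not. The inputs do not generate 37, but 37 satisfies every stated requirement.

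Nor is this a matter of a condensed article leaving detail to a fuller document: the completers, the rate, the factor, the result and the primary test are all printed.

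**Conclusion.** The point holds as a mismatch between the inflation factor and the loss it is meant to cover. From 24 completers and 20% drop-out the recruitment number is 30; the printed 37 comes from a factor meant for diluted effects. The size is about 7 patients, or 23% more than the stated assumptions justify, in the conservative direction.

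The value of 30 rests only on the plan's own 24 and 20% and on a primary test that needs a value after both treatments. The power figures rest further on a fall of 4.2 μmol/L, a within-person SD of 4 μmol/L and a two-sided 5% test; the last of these is an assumption. A stated figure needs correcting; the trial's ability to answer its question is not in doubt.

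**What to change.** Correct the sample-size sentence in one of two ways:

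- Use the factor 1/(1 − 0.20) and state 24/0.8 = 30, changing the abstract to match.
- Keep 37, and state that at 20% drop-out it yields about 29 completers with about 97% power, or that it tolerates about 35% loss before falling to 24. Then name what the margin is for, such as non-adherence, antibiotic exclusions or a within-person SD above 4 μmol/L.

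The second keeps the margin and leaves the abstract unchanged. In either case correct or remove the misprinted 1/1(1-υ)^2. If a squared factor is kept, present it as an allowance for dilution and say which participants would be analysed with a diluted effect.

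The cost is a sentence or two of text, plus the number in the abstract if it changes. No extra patients are needed and the analysis is unchanged.

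### The primary t-test is valid and adequately powered, but it uses two of seven IS values and drops patients without a period-2 end value; a mixed model as primary would use them at almost no cost

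*Protocol article*

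**What the plan says.** The primary test, in the Statistical analysis section of the protocol article, compares the two sequence groups on one difference per patient: "independent t-test with treatment sequence allocation as the independent variable and the difference between serum concentrations measured after the first and second treatment". The next sentence ranks a model-based analysis second: "Secondary analysis of the primary outcome will include mixed modelling to account for missing data and to determine whether there is a dose dependent effect". It does not say whether the values taken before each period enter that model.

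On sampling, the Serum indoxyl sulphate section states: "Venous blood will be collected following an overnight fast at 7 time points throughout the study". Table 2 places these at run-in (week −2) and at weeks 0, 3, 6, 11, 14 and 17.

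On size, the planning mean comes from a cohort in the same department: "The mean serum concentration of IS in this population was 14 μmol/L". For variability, the section uses that cohort's "mean intra individual standard deviation of 4 μmol/L between 3 measurements over a 6 week period". The article adds: "This sample size is based on a 30% reduction in IS levels", at 5% alpha and 90% power. This gives 24 completers. An allowance for 20% dropout, with the factor squared, brings recruitment to 37.

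**The concern.** The dependent variable is one difference per patient, week 6 against week 17. The values at weeks 0, 3, 11 and 14 play no part in the primary result. A patient who completes period 1 and then leaves contributes nothing to it, even with a full baseline and first-period record. The plan expects 20% to drop out and already names a method for missing data, but ranks it second.

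The target effect is also proportional (30%), whereas the test is described on concentrations. If the effect is proportional, the absolute fall scales with each patient's level, and this adds variance to the raw differences.

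At stake is some precision from data that will be collected anyway, and a primary result that leaves out some randomised patients.

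**Working it through.** **1. The plan's own figure.** Inputs from the Statistical analysis section: mean 14, within-patient SD 4, 30% reduction. A two-sided 5% test is assumed.

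- Effect δ = 0.30 × 14 = 4.2 μmol/L.
- SD of a within-patient difference = 4 × √2 = 5.66.
- With n completers per sequence, SE(δ) = ½ × 5.66 × √(2/n).
- n = 11 (22 in total): SE 1.206, power 91.2% by the non-central t.
- n = 12 (24 in total): SE 1.155, power 93.5%.
- n = 15 (30 in total): SE 1.033, power 97.5%.

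The stated 24 is therefore reproduced with a little to spare. For recruitment, 24 / 0.8² = 37.5, which matches 37. With 20% loss, 37 × 0.8 = 29.6, so about 30 would complete.

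**2. Common drift.** Let π₁ and π₂ be the period means and δ the treatment effect. The expected difference is (π₁ − π₂) + δ in one sequence and (π₁ − π₂) − δ in the other. Subtracting leaves 2δ, so a shared period effect cancels.

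**3. Variance with all the data.** Per sequence: 37 × 0.8 / 2 = 14.8 completers and 3.7 dropouts. Visits: weeks 0, 3, 6, 11, 14, 17, each with its own mean, and a treatment effect after 3 and after 6 weeks. Covariance: between-patient variance 8² (assumed) plus 4² times a correlation matrix R. R is either the identity or exp(−lag/τ) with τ of 10 or 20 weeks, with or without 30% pure measurement noise (all assumed). The variance of the six-week effect is its diagonal element of [Σ n X′V⁻¹X]⁻¹, divided here by the variance of the completer t-test under the same V. For the last column, the ratio is 1 − ρ², where ρ is the correlation between the baseline difference and the end-value difference.

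| Serial correlation | Model, dropouts leave after week 6 | Model, dropouts leave between weeks 3 and 6 | Completers, adjusted for baseline difference |
|---|---|---|---|
| None | 0.922 | 1.000 | 1.000 |
| τ = 10 | 0.818 | 0.861 | 0.947 |
| τ = 10, 30% noise | 0.886 | 0.952 | 0.980 |
| τ = 20 | 0.744 | 0.779 | 0.894 |
| τ = 20, 30% noise | 0.880 | 0.947 | 0.974 |

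The variance falls by 8-26%, 0-22% and 0-11% respectively. Between-patient SDs from 2 to 10 move the two model columns by about 0.02 at most. The last column is unaffected, because stable differences between patients cancel. A stronger link would give more: ρ = 0.5 means 1 − 0.25 = 0.75. The article gives no value of ρ.

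A mixed model of the end values alone, with 30 completers and 7 period-1-only patients, gives ratios of about 0.92-0.98, a gain of 2-8%.

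**4. Raw against log scale.** Simulation of 20,000 trials: 24 completers, log-normal values, within-patient CV 4/14 = 0.29, true proportional fall of 30%.

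| Between-patient CV (assumed) | Power, raw | Power, log |
|---|---|---|
| 40% | 97% | 99% |
| 60% | 94% | 99% |

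**The case against.** The strongest reply is that nothing is broken. The sequence t-test is the standard valid test for this design. The trial was sized on completers, and the squared dropout factor is more generous than the ordinary one (24 / 0.8 = 30), so excluding dropouts is already paid for: power is 93.5% at 24 completers and 97.5% at 30. All of this stands.

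A within-patient difference already removes stable differences between patients, so with equal within-patient correlations the period baselines add nothing for completers. The larger gains need serial correlation, and in part dropout late enough to leave a week-6 value. The table treats the covariance as known, while in practice it is estimated from about 37 patients. This also stands, and it is why the gain is given as a range that can start at zero.

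Bias from using completers looks small. With dropout driven by the week-6 value, a true effect of 4.2 was estimated as 3.96 to 4.19 under assumed strengths of dependence. The article does not address transformation, which the analysis plan may settle.

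Two stronger readings are tempting and are not supported:

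- A reader might infer that drift in a progressive disease over 17 weeks goes unadjusted. Step 2 shows that common drift cancels; only patient-specific drift remains.
- A reader might infer that the mixed model as planned would recover the baseline information. The article ties that model to missing data and dose dependence and does not say that the baselines enter.

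What remains against the reply is that the data are collected anyway, and that the choice of primary analysis is stated in the article.

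**Conclusion.** The primary test is valid, adjusts for a common period effect and meets its power target. It nevertheless sets aside the IS values at weeks 0, 3, 11 and 14 and every patient without a period-2 end value. Using them lowers the variance of the six-week effect by about 8-26% if the 20% leave after completing period 1, and by 0-22% if they leave between weeks 3 and 6. Adjusting completers for the baseline difference alone gives 0-11%. The log scale lifts power at 24 completers from about 94-97% to about 99%.

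These figures assume a between-patient SD of 8, the serial correlations listed, between-patient CVs of 60-40% for the log comparison, and a truly proportional effect. None of these is given in the article. The change is worth making because it is nearly free. It does not follow that the trial is underpowered or that its primary result would be wrong.

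**What to change.** Make the primary analysis a mixed model of log IS in all randomised patients with any IS data. Include patient as a random effect, period-by-visit means, a treatment effect at mid point and at end point, and the week 0 and week 11 values in the model. The treatment contrast after six weeks (weeks 6 and 17) is the primary estimate, reported as a ratio of geometric means so that it matches the 30% target. Keep the sequence t-test on completers as a sensitivity analysis. If the t-test stays primary, adjust it for the baseline difference (week 0 minus week 11).

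The cost is a change of wording, with no new visits or samples. The downsides are a slightly more complex model, a covariance estimated from about 37 patients, and reliance on the washout having cleared any treatment effect from the week-11 value. The covariance structure should be fixed before unblinding.
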